### Study Population

The study will enroll AGYW aged 15-24 years who meet the inclusion criteria outlined in Table 1. To align with the study objectives, eligibility is limited to AGYW who are current LARC users or have an existing interest in LARC, thereby focusing the study on a population for whom integrated LARC and LAI-PrEP services are most relevant while allowing assessment of variation in awareness, perceptions, and willingness to use LAI-PrEP. Up to 220 AGYW will be recruited across the three study sites to participate in the quantitative component through structured surveys. A subset of the AGYW participants will be invited to join up to three FGDs, each with approximately 10 AGYW, to explore further the attitudes, preferences, and willingness to use integrated LARC and LAI-PrEP services. In parallel, up to 20 key informants (KIs) who are stakeholders in reproductive health and HIV prevention and who meet eligibility criteria will participate in IDIs to characterize stakeholder perceptions, practices, and norms that influence the adoption of integrated services. The KI sample will include up to three individuals from each of the following groups, specifically: AGYW peers (including sex workers and social media influencers), local health authorities, health care professionals, community leaders, representatives from reproductive health and HIV prevention organizations, and representatives from civil society. These stakeholders were selected for their direct involvement in shaping service delivery.

Exclusion criteria include any condition that, in the opinion of the study team, would preclude informed consent, make study participation unsafe, complicate interpretation of study outcome data, or otherwise interfere with achieving the study objectives. This general exclusion applies to all participant groups. For AGYW survey participants only, additional exclusions include known HIV-positive status, confirmed through the most recent health record (eg, health passport, HIV test card, or similar document) or by self-report if health records are not available.

Potential participants will be recruited from three selected KCCA clinics. Eligible AGYW will be identified through clinic records and service points, particularly LARC and HIV prevention programs. Community-based outreach will complement clinic recruitment, leveraging peer networks, community health workers, and targeted informational sessions to engage AGYW with diverse experiences. A peer-led snowball sampling approach will facilitate recruitment by encouraging initial participants to refer peers from their social networks. Recruitment will also extend to informal settlements and venues associated with sex work, such as bars and lodges, where AGYW are particularly vulnerable. Collaborations with venue managers and health centers will enable outreach to this population, ensuring equitable access to LARC and LAI-PrEP. Community sensitization events will educate AGYW on reproductive health, HIV prevention, and LARC and LAI-PrEP services. Study staff will identify and recruit KIs. The recruitment phase is expected to span approximately 4-6 months. A summary of study components, target populations, and methodologies is presented in Table 1.

**Table 1 table1:** COMPASS study components, populations, methods, and eligibility criteria.

Study component	Target population	Method and data collection tool	Key measures and focus areas	Eligibility
Quantitative survey	AGYW^a^ aged 15-24 years attending selected KCCA^b^ health facilities	Structured questionnaire	Demographics, reproductive health history, preferences and willingness to use LARC^c^ and LAI-PrEP^d^, awareness and attitudes, perceived barriers and facilitators	Aged 15-24 years at enrolment. HIV-negative by rapid testing per national algorithm. Able and willing to provide written informed consent (parental waiver approved). Current use of LARC for ≥1 month or interest in LARC and PrEP or LAI-PrEP. Willing to comply with study procedures.
FGDs^e^	Subset of surveyed AGYW	Semistructured discussion guide	In-depth exploration of motivations, perceptions, social influences, and contextual factors affecting uptake and adherence to LARC and LAI-PrEP	Participated in quantitative survey component
IDIs^f^	Key stakeholders: health care providers, community leaders, peer educators, and program implementers	Interview guide	Perceptions of integrated service delivery, operational challenges, community norms, provider readiness, and system-level facilitators and barriers	Aged ≥18 years (see Study Population section for key informant details)

^a^AGYW: adolescent girls and young women.

^b^KCCA: Kampala Capital City Authority.

^c^LARC: long-acting reversible contraception.

^d^LAI-PrEP: long-acting injectable preexposure prophylaxis.

^e^FGD: focus group discussion.

^f^IDI: in-depth interview.

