### Sample Size and Sampling Procedures

The quantitative sample size of up to 220 AGYW was estimated using the Kish-Leslie formula [51], assuming an 85% acceptability of LARC and LAI-PrEP if these services were made available. This sample size enables robust estimation of preferences, attitudes, and willingness to use integrated services, while accounting for variability in uptake across the study population. Participants will be purposively selected from the three KCCA clinics to ensure representation across urban, suburban, and peri-urban settings. For FGDs, a subset of 30 AGYW who completed the quantitative survey will be selected using stratified purposive sampling to ensure diversity in age, LARC and PrEP experience, and socio-demographic characteristics. This approach will enable in-depth exploration of factors influencing uptake and adherence. KIs will also be purposively sampled to capture a wide range of perspectives, professional roles, and influence over reproductive health and HIV prevention services. This combined sampling approach ensures a comprehensive understanding of both individual-level experiences and community-level factors affecting the integration and uptake of LARC and LAI-PrEP among AGYW in Uganda.

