Logistic regression models will be used to identify predictors of high acceptability and willingness to use integrated LARC and LAI-PrEP services. Variables considered clinically or theoretically relevant, together with those demonstrating an association at the bivariate analysis stage (*P*<.20), will be considered for inclusion in the multivariable models. Potential confounders, including age, education, socioeconomic status, marital status, prior contraceptive use, and HIV prevention history, will be retained in the final models where appropriate, based on subject-matter knowledge and statistical significance. Multicollinearity among independent variables will be assessed using variance inflation factors (VIFs) and correlation matrices. Where scientifically justified, interaction effects (for example, between age group and prior contraceptive use) will be explored by including interaction terms in the regression models. Model fit and assumptions will be evaluated using appropriate diagnostic procedures, including goodness-of-fit tests and assessment of influential observations. Adjusted odds ratios (aORs) with 95% CIs will be reported, and statistical significance will be assessed at a 2-sided α level of .05. Comparative analyses using 2-tailed *t* tests or ANOVA will further explore differences in preferences and attitudes across subgroups, including younger (15-19 years) versus older (20-24 years) AGYW and rural versus urban participants. For clarity of interpretation, results will be presented in tables summarizing numerical data and key statistics, including odds ratios (ORs) and *P* values. They will be visually illustrated with bar charts, pie charts, and histograms. Clustered bar charts and box plots will be used to highlight subgroup differences and significant predictors. This combined descriptive, inferential, and visualization approach will provide a robust understanding of AGYW preferences and attitudes toward LARC and LAI-PrEP, identify key facilitators and barriers to their uptake, and reveal demographic and behavioral predictors of positive engagement with these prevention methods.

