## Results

The study was funded in February 2026. Ethical and regulatory approvals were obtained before study initiation. Study preparation, including site initiation, staff training, finalization of study instruments, and community sensitization, was completed before participant recruitment. Participant recruitment began in March 2026 and was completed in July 2026, at selected KCCA clinics and community settings. A total of 220 AGYW and 20 KIs were enrolled, and both quantitative and qualitative data collection were completed in July 2026. Data cleaning and quality assurance activities were ongoing, and quantitative and qualitative data analyses were planned following completion of data collection. No major protocol modifications have been made since study initiation. Study findings are anticipated to be submitted for publication in 2027, following completion of data analysis and manuscript preparation.

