Participant recruitment may also be subject to selection bias because clinic-based recruitment may preferentially enroll AGYW who are already engaged with health services, while peer-led snowball sampling may overrepresent individuals within existing social networks. To reduce this potential bias, the study incorporates community-based recruitment through peer networks, community health workers, community sensitization activities, and outreach beyond clinic settings, in addition to recruitment across three KCCA clinics that serve different populations: Kisenyi (urban), Kawaala (peri-urban), and Komamboga (suburban). Although these approaches are intended to broaden participant representation, some residual selection bias may remain.

Additionally, reliance on self-reported measures regarding sexual behavior, contraceptive use, and PrEP adherence may be affected by recall and social desirability bias [73-75]. Mitigation strategies, including confidential data collection methods and triangulation across multiple data sources, are built into the design to reduce these risks. Nonetheless, these limitations provide opportunities for future work, including follow-up studies to assess the applicability of identified strategies in rural contexts and longitudinal evaluations to determine their impact on sustained uptake and adherence. Future directions will also include pilot testing of co-designed interventions to refine their feasibility, cost-effectiveness, and scalability across diverse service delivery settings.

The evolving global HIV prevention funding and policy landscape further reinforces the significance of this research. Recent reductions and policy shifts in funding for the President’s Emergency Plan for AIDS Relief (PEPFAR) and the United States Agency for International Development (USAID) have heightened the emphasis on cost-efficiency, sustainability, and local ownership in HIV programming [76,77]. Although this study is not expected to be directly affected by these funding shifts, its focus on community-driven and contextually relevant implementation approaches aligns with global priorities to optimize resources and strengthen health systems.

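### Some women are recruited through peer chains and venues, but the named tests make no allowance for within-chain correlation, so standard errors are too small for predictors that a chain shares

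*Protocol article*

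**What the plan says.** **Recruitment.** The Study Population section starts from clinic files and points of service, and adds outreach as a supplement. Two of the added routes bring in women who may know one another: "A peer-led snowball sampling approach will facilitate recruitment by encouraging initial participants to refer peers from their social networks", and "Recruitment will also extend to informal settlements and venues associated with sex work, such as bars and lodges". The share of women from each route, the number of chains and their length are not given.

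**Outcome.** Under Data Collection, the composite acceptability score sums three items. Two of them concern comfort within the community and how acceptable peers are thought to find the methods.

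**Analysis.** The Data Analysis section names Pearson or Spearman correlations, chi-square tests, t tests/ANOVA and logistic regression with a P<.20 screen. "Adjusted odds ratios (aORs) with 95% CIs will be reported", and "statistical significance will be assessed at a 2-sided α level of .05". The confounders it names are individual traits: age, education, socioeconomic status, marital status, contraceptive history and HIV prevention history. The checks it names are collinearity, goodness of fit and influential observations.

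**Limitations.** Under Anticipated Findings, the article accepts that "peer-led snowball sampling may overrepresent individuals within existing social networks", and treats this as selection bias only.

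**Status.** The Results section reports: "A total of 220 AGYW and 20 KIs were enrolled". Data collection is complete and analysis is still to come.

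**The concern.** Each named method, in its ordinary form, treats the 220 women as independent. Women referred by friends, or reached at the same venue, may share background and attitudes. Two of the three acceptability items ask them to rate what may be partly the same community and the same peers. If both outcome and predictor are alike within a chain, the sample holds less information than 220 separate women, and the ordinary standard error is too small.

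This is a different matter from selection bias. Adjusting for recruitment route may reduce bias between routes, but it does not correct a standard error for correlation inside a chain.

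At stake is which characteristics are reported as predictors of acceptability and willingness. The most exposed are those that friends tend to share. Among those the plan names, socioeconomic status, marital status, age group and the comparison by residential setting are plausible candidates.

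**Working it through.** **1. The plan's own figure.** "The quantitative sample size of up to 220 AGYW was estimated using the Kish-Leslie formula", "assuming an 85% acceptability of LARC and LAI-PrEP if these services were made available". The formula is n = 1.96² × p(1−p)/d². The precision d and any non-response allowance are not stated, so 220 cannot be derived from the article's inputs alone.
- With d = 0.05 (assumed): 3.8416 × 0.85 × 0.15 / 0.0025 = 195.9, so 196. With 10% non-response (assumed): 196/0.90 = 218.
- With no inflation, 220 corresponds to d ≈ 0.047.

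None of these variants needs a design effect, so 220 is consistent with a calculation for independent women.

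**2. Formula for the error.** Let s be the share of women in chains, m the chain length, and ICC_y and ICC_x the within-chain correlations of the outcome and the predictor.
- Design effect: DEFF = 1 + s(m−1) × ICC_y × ICC_x
- True two-sided error of a nominal 5% test: 2 × [1 − Φ(1.96/√DEFF)]
- Factor by which intervals are too narrow: √DEFF

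**3. Assumed inputs.** None is in the article: s = 0.25 to 0.5, m = 5 to 10, latent outcome correlation 0.2 to 0.3. For an outcome split at its median, the correlation on the yes/no scale is (2/π) × arcsin(latent value), which gives 0.128 and 0.194.

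**4. Results.** *Partly shared* means a yes/no predictor with latent correlation 0.3, so ICC_x = 0.194. *Fully shared* means ICC_x = 1.

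| s | m | ICC_y | Predictor | DEFF | True error |
|---|---|---|---|---|---|
| any | any | any | varies freely (ICC_x = 0) | 1.00 | 5.0% |
| 0.25 | 5 | 0.128 | partly shared | 1 + 0.25×4×0.128×0.194 = 1.025 | 5.3% |
| 0.5 | 10 | 0.194 | partly shared | 1 + 0.5×9×0.194×0.194 = 1.169 | 7.0% |
| 0.25 | 5 | 0.128 | fully shared | 1 + 0.25×4×0.128 = 1.128 | 6.5% |
| 0.5 | 10 | 0.194 | fully shared | 1 + 0.5×9×0.194 = 1.873 | 15.2% |
| 1 | 10 | 0.194 | fully shared | 1 + 9×0.194 = 2.746 | 23.7% |

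Simulation under these assumptions (220 women, no true effect) agrees to within about a percentage point: 7-16% for fully shared predictors with a quarter to half in chains, and about 25% at the extreme. The partly shared range depends on how strongly the predictor is shared. With ICC_x = 0.5 in the least favourable of these cases, DEFF = 1 + 0.5×9×0.194×0.5 = 1.44 and the error is about 10%.

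**5. Interval width.** Intervals are too narrow by √1.025 to √1.169, or 1.01 to 1.08, for partly shared predictors. For fully shared ones the factor is √1.128 to √1.873, or 1.06 to 1.37.

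**6. The P<.20 screen.** At DEFF 1.5 a predictor with no effect passes with probability 2 × [1 − Φ(1.2816/√1.5)], about 30% instead of 20%.

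**7. Effect of the remedy.** In the same simulations cluster-robust errors brought the rate back to roughly 5-8%. It stays somewhat above nominal when long chains leave few clusters.

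**The case against.** The strongest reply is that the article never says women will be analysed as independent. Logistic regression does not fix the variance estimator, the list of model checks is open-ended, and a fuller plan could specify robust errors. This stands in part: independence is inferred from the named methods. But the section goes down to screening thresholds and diagnostics, and what it names does not match the sampling it describes. Carried out as written, it gives standard errors that are too small wherever chains share outcome and predictor.

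The second reply is that the effect may be small. This stands. Outreach supplements clinic recruitment, so a sample made up wholly of chains is unlikely. With a quarter of women in chains of 5 and a latent correlation of 0.2, the error is about 5% for a partly shared predictor and 6.5% for a fully shared one. At the 85% acceptability assumed for sample size, instead of a median split, the latter falls to about 6.1%.

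The third reply concerns two inferences that a reader might draw. One is that predictors such as sex work or venue will carry the worst error rates. Neither is a named predictor, and nothing shows that any named trait is constant within a chain. The other is that false predictors pass straight into the behaviour change strategies. The Data Analysis section builds the COM-B mapping mainly from qualitative themes, and survey results join at interpretation. Neither inference is supported.

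**Conclusion.** The concern holds in a limited, conditional form. The named analysis does not allow for correlation within referral chains or venues, and so understates standard errors for predictors that women in one chain share.

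On the assumptions above, with a quarter to half of women in chains, the true error of a 5% test is about 5-7% for partly shared predictors, nearer 10% if sharing is strong and chains are long and common. It is 7-16% for predictors common to a whole chain. A reader might quote about 25% as the expected error. That requires every woman to come in a chain of 10 and a predictor identical within each chain, and the recruitment text does not support it. The article fixes none of the inputs, so the actual effect could be negligible. It is still worth correcting, because the direction is known and the analysis has not been done.

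**What to change.** **Where referrer or venue was recorded.** Add to Data Analysis, before analysis begins:

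> Logistic models and subgroup comparisons will use cluster-robust standard errors grouped on referral seed or recruitment venue. Each woman belongs to one group, assigned by a rule set before analysis; women recruited directly form single-member groups.

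The rule must cover women who belong to both a chain and a venue. The chi-square and t test/ANOVA comparisons can be run as one-predictor regressions with the same grouping. Grouping on clinic is no substitute: three clusters are too few for robust errors.

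**Where it was not recorded.** The article describes no log of referrers, so this may be the case. State the independence assumption as a limitation, and describe P values and intervals as likely optimistic for traits that peers share. A proxy such as clinic by route by enrolment week can split one chain and pool unrelated women, so show it only as a sensitivity analysis.

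**Cost.** One grouping variable and one option in the Stata code if the information exists; otherwise a sentence or two. Some intervals widen, mostly slightly and more for predictors that whole chains share. If chains were few and short, little changes.

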### Sample Size and Sampling Procedures

The quantitative sample size of up to 220 AGYW was estimated using the Kish-Leslie formula [51], assuming an 85% acceptability of LARC and LAI-PrEP if these services were made available. This sample size enables robust estimation of preferences, attitudes, and willingness to use integrated services, while accounting for variability in uptake across the study population. Participants will be purposively selected from the three KCCA clinics to ensure representation across urban, suburban, and peri-urban settings. For FGDs, a subset of 30 AGYW who completed the quantitative survey will be selected using stratified purposive sampling to ensure diversity in age, LARC and PrEP experience, and socio-demographic characteristics. This approach will enable in-depth exploration of factors influencing uptake and adherence. KIs will also be purposively sampled to capture a wide range of perspectives, professional roles, and influence over reproductive health and HIV prevention services. This combined sampling approach ensures a comprehensive understanding of both individual-level experiences and community-level factors affecting the integration and uptake of LARC and LAI-PrEP among AGYW in Uganda.

### Study Procedures

AGYW who express interest and meet the eligibility criteria will be consecutively enrolled at the designated health centers, enrolment and recruitment sites, which serve as key points for accessing reproductive health and HIV prevention services. Potential participants referred through community sensitization activities will first receive information about LARC and LAI-PrEP. Those expressing interest and meeting initial eligibility criteria will then undergo a screening process to confirm eligibility. Eligible participants will be taken through the informed consent process by trained study staff and, upon enrolment, assigned a unique study identifier to maintain confidentiality. Demographic information and quantitative data will be collected using structured paper-based questionnaires administered to AGYW.

We will endeavor to include AGYW aged 15-19 years and 20-24 years at a minimum ratio of 1:1.5 to ensure balanced age representation. We will also ensure diverse representation across socioeconomic statuses and educational backgrounds, providing a comprehensive understanding of preferences and perspectives across subpopulations.

Following the quantitative assessments, FGDs will be conducted to allow for a more in-depth exploration of key themes. FGDs will take place at the KCCA clinics to ensure accessibility and familiarity for participants. Sessions will be conducted in either English or Luganda, depending on participants’ language preferences, and will last approximately 90 minutes. Three FGDs will be held with AGYW, stratified by age groups (15-17, 18-20, and 21-24 years), with each participant completing a single FGD with others in the same age group. FGD guides will undergo pilot testing with a subset of the target population to ensure clarity, cultural appropriateness, and relevance. Before completing the FGD, participants will receive an introduction to LARC and LAI-PrEP as outlined in the FGD Guide. FGDs will be co-facilitated by trained AGYW peers to foster relatability, inclusivity, and alignment with Community-Based Participatory Research principles [52,53]. IDIs will be conducted among KIs enrolled in the study. Each key informant will complete a single IDI. Prior to the interview, participants will receive an introduction to LARC and LAI-PrEP, as outlined in the IDI Guide. Interviews will be conducted at participants’ workplaces to prioritize convenience and comfort, in either English or Luganda, depending on language preference, and will last approximately 60 minutes. The overall flow of study activities is summarized in SPIRIT (Standard Protocol Items: Recommendations for Interventional Trials) style schematic (Figure 2), which outlines the sequence of activities from community entry and participant enrolment through data collection, analysis, and dissemination [54].

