## Methods

### Study Design

The COMPASS study will use a mixed methods, cross-sectional implementation science design. This study will use 3 data collection approaches (structured surveys, focus group discussions [FGDs], and in-depth interviews [IDIs]) to generate both quantitative and qualitative evidence on integrated LARC and LAI-PrEP services. Initially, quantitative data will be collected through structured surveys administered to AGYW attending selected health facilities in Kampala to assess their attitudes, preferences, and willingness to use LARC and LAI-PrEP (Multimedia Appendix 1). Qualitative data will be gathered through FGDs among a subset of surveyed AGYW to explore further perceptions and motivations influencing uptake in a group setting (Multimedia Appendix 2), and through IDIs with key stakeholders, including health care providers, community leaders, and program implementers, to provide detailed perspectives on the social, cultural, and health system factors that may influence the adoption of integrated services. Taken together, these approaches provide a layered understanding of both AGYW’s preferences and the broader contextual factors shaping uptake (Multimedia Appendix 3).

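### Survey recruits with differing stated prior information are pooled, and neither clinic nor recruitment route is among the named adjustment or subgroup variables

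*Protocol article*

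**What the plan says.** Study Population sets out several ways into one survey sample. For the clinic route, "Eligible AGYW will be identified through clinic records and service points, particularly LARC and HIV prevention programs". Community outreach, peer-led snowball referral and sensitization events that teach about both products are added, and "Recruitment will also extend to informal settlements and venues associated with sex work, such as bars and lodges".

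Study Procedures then says: "Potential participants referred through community sensitization activities will first receive information about LARC and LAI-PrEP". Screening, consent and the questionnaire follow. No matching step is stated for clinic, peer or venue recruits.

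Awareness and attitudes are survey measures in Table 1, and understanding and acceptability are in Table 2. Data Collection makes acceptability the primary outcome.

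In Data Analysis the named adjustment variables are "Potential confounders, including age, education, socioeconomic status, marital status, prior contraceptive use, and HIV prevention history". Other variables may enter on relevance or a bivariate P<.20. One interaction is given as an example (age group by prior contraceptive use), and two subgroup contrasts are named: younger versus older, and rural versus urban.

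The sample is described in different ways. Study Design speaks of "structured surveys administered to AGYW attending selected health facilities in Kampala", Table 1 likewise refers to facility attenders, and Sample Size and Sampling Procedures has women selected from the three clinics. Study Population and Results describe clinics plus community settings.

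**The concern.** The abstract names low awareness as a barrier to uptake, and the Conceptual Framework counts knowledge as part of Capability. If some women are taught about the products by the study shortly before answering, their awareness is a post-information measurement. Pooled with answers from women who may not have been taught, it yields a figure that describes neither group and moves with the share of each.

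Willingness can move in the same way, because route may also go with risk, age, marital status and existing contact with services. The regression results are affected too: if route is related both to a covariate and to the outcome, leaving it out lets the covariate carry part of the route effect.

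The three clinics were chosen because their settings differ, yet no named analysis compares them. The one geographic contrast uses categories that do not correspond to the sites.

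**Working it through.** **1. The plan's own figure and the margin it implies.** The article states: "The quantitative sample size of up to 220 AGYW was estimated using the Kish-Leslie formula", "assuming an 85% acceptability of LARC and LAI-PrEP if these services were made available". The formula is n = z²p(1−p)/d², with z = 1.96 and p = 0.85. The margin d and any non-response allowance are not stated.
- d = 0.05 gives 195.9, so 196. With an assumed 10% non-response, 196/0.9 = 217.8, so 218.
- d = 0.047 without inflation gives 222.

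The figure of 220 is compatible with ordinary inputs but cannot be reproduced from those given. Nothing below depends on that. The half-width at n = 220 is 1.96 × √(0.85 × 0.15/220) = 0.047, or 4.7 points, treating the sample as a simple random one.

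**2. Effect of the recruitment mix on a pooled proportion.** Let s be the share informed through sensitization, p₁ their rate and p₀ the rate in the others. Then pooled = s·p₁ + (1−s)·p₀. Moving s from 20% to 80% shifts the pooled figure by 0.6 × (p₁ − p₀). The article gives none of these values, so all are assumed.

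| Measure | p₀ / p₁ | s = 20% | s = 80% | Shift (points) |
|---|---|---|---|---|
| Willingness | 80% / 90% | 82.0% | 88.0% | 6.0 |
| Willingness | 75% / 92% | 78.4% | 88.6% | 10.2 |
| Awareness | 40% / 80% | 48% | 72% | 24 |
| Awareness | 30% / 90% | 42% | 78% | 36 |

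Over this range of shares, the shift exceeds the 4.7-point margin once the routes differ by more than 4.7/0.6 = 7.9 points. With a smaller gap or a narrower range of shares it may not. The sign could also reverse.

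This arithmetic does not apply to the proportion with high acceptability. That category is cut at the observed median, so its pooled share is largely fixed by construction.

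**3. Effect on associations.** Take a covariate with no effect of its own. Assume the route share differs 60/40 between its levels and the outcome differs 60/40 between routes.
- The outcome rates by covariate level are 0.6×0.6 + 0.4×0.4 = 0.52 and 0.4×0.6 + 0.6×0.4 = 0.48.
- The crude odds ratio is (0.52/0.48)/(0.48/0.52) = 1.17.
- With 70/30 for both, the rates are 0.58 and 0.42 and the odds ratio is 1.91.

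These are illustrations. Adjustment for the listed confounders would remove some of the effect.

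**4. What the models can carry.** If 85% is applied to willingness, non-events number 220 × 0.15 = 33. Count one parameter for each of the six named confounders.
- Named confounders only: 33/6 = 5.5 non-events per parameter.
- Plus clinic (two parameters): 33/8 = 4.1.
- Plus a two-level route indicator: 33/9 = 3.7.
- With a four-level route instead: 33/11 = 3.0.

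The acceptability model has more room. If the median split is near even, 110/9 = 12.2 per parameter with clinic and a two-level indicator. Ties on the summed score could make the split less even.

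**5. Geographic contrast against the sites.** Study Setting describes one urban, one peri-urban and one suburban clinic. The Discussion treats rural areas as a setting to which findings may not transfer. Table 2 collects residence, so women could be classified by it, but a rural-versus-urban split would still not compare the three settings the sites were chosen to represent.

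**The case against.** The strongest reply is that this is a condensed article whose lists are illustrative. The confounders are introduced as examples, theoretically relevant variables may enter, and a full analysis plan may name clinic or route. That stands as far as silence goes: the article does not rule out such adjustment. But it does fix a geographic contrast that does not fit its sites and describes its sample inconsistently. The P<.20 screen would not guarantee that clinic or route enters.

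Second, risk is partly handled. HIV prevention history, prior contraceptive use, socioeconomic status and marital status are listed, and partners, condom use and recent STI are collected. That stands for risk; it does not cover unequal prior information.

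Third, the Discussion already discloses selection bias from clinic and snowball recruitment and disclaims external validity as an aim. That is fair, but its remedy is more recruitment routes, and it does not mention prior information.

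A reader might infer three stronger things that the documents do not support:
- **That other routes were uninformed.** The article does not say so. Clinic women come largely from LARC and HIV prevention programs, and community sensitization preceded recruitment, so they may have been exposed too.
- **That only sensitized women were filtered on interest.** Study Procedures applies expressed interest to all enrolled women, and Table 1 requires current LARC use or interest whatever the route.
- **That awareness and acceptability are shown to reflect the recruitment mix.** Route-specific rates and shares are unknown, and clinic women could be the more willing group.

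**Conclusion.** The point holds in a limited form. Women are pooled across routes for which the article states different pre-survey information, and awareness and understanding are among the things measured. The named analyses include neither clinic nor route, and the rural/urban contrast does not match the clinic settings. Pooled awareness and willingness may therefore depend partly on the recruitment mix.

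The size cannot be derived from the document. The willingness illustrations give about 6 to 10 points against a 4.7-point sampling margin. They rest on assumed gaps of 10 and 17 points between routes and an informed share varying from 20% to 80%. Awareness could move more if teaching affects it strongly. It is worth settling now: Results reports data collection complete and analysis still planned.

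**What to change.** - Include clinic (three levels) in the multivariable models, and replace the rural-versus-urban comparison with one by clinic setting.
- Where route was recorded, report awareness, acceptability and willingness by route, or at least by whether the study had informed the woman before the survey. Label awareness in pre-informed women as post-information.
- Add a two-level route or prior-information indicator to the acceptability model. In the willingness model use it only as a sensitivity analysis, because of the few non-events.
- Describe the sample as clinic plus community recruits in Study Design, Table 1, and Sample Size and Sampling Procedures, in line with Study Population and Results.

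The cost is two or three more parameters, slightly wider confidence intervals and one extra table. Intervals may widen more in the willingness model, where non-events are sparse. The clinic changes and the rewording do not depend on route data. The route analyses do: the article does not say that route was logged, and since recruitment has closed it may not be recoverable. If it is not, the report should say so and state that awareness was measured partly after study-provided information.
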